**Data analysis**

Statistical analysis will be performed using SPSS 26.0, Graphpad Prism Software, and for quantitative data, the results will be presented as mean ± standard deviation (x ± s) or median (m) and interquartile range (IQR), between-group comparisons will use Welch's t-test or Wilcoxon's rank-sum test; categorical data will be presented as frequencies or percentages, and between-group comparisons will use the chi-square test or Fisher's exact probability method, time-to-event variables will be estimated using the Kaplan-Meier method, compared using the log-rank or generalized rank-sum test methods, and Cox regression models will be established, with P values less than 0.05 considered statistically significant.

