**Randomization**

Patients with acute ST-elevation myocardial infarction reperfusion who met the inclusion criteria and signed an informed consent will be randomized by coin toss. With the coin heads up, patients with acute ST-elevation myocardial infarction reperfusion will be assigned to the extracorporeal shock therapy group. With the coin heads down, patients with acute ST-elevation myocardial infarction reperfusion will be assigned to a blank control group.The test group and the control group will be divided into 1:1 proportional grouping. In order to ensure blinding, the details of the random assignment will not be given to the investigator. In addition, Shock wave treatment practitioners and evaluators will be completely separated.

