**Sample size estimation**

This study is a randomized controlled trial. The experimental group will be received extracorporeal cardiac shock wave therapy intervention, while the control group will be received conventional treatment for acute myocardial infarction. The left ventricular ejection fraction (LVEF) of the study object is one of the observed outcome indicators. According to the literature review results, the average LVEF in the control group is 58.0 ± 11.7 points. It is estimated that LVEF in the shock wave intervention group can be increased by 8.1%,α= 0.05, and the assurance is 90%. Calculate the sample size according to the following sample size calculation formula

[figure not shown]

44 cases can be calculated, considering 1:1 randomization, that is, 44 cases in the intervention group and 44 cases in the control group, and considering 15% will lost to follow-up and refuse to visit, finally, at least 51 subjects in the intervention group and 51 subjects in the control group will be needed, and a total of at least 102 subjects will be included.

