
**Data collection and follow-up**

All necessary data will be collected and recorded in electronic case report forms for this study, which will be mainly obtained from medical records(such as electronic or paper medical records), local laboratory testing records and investigator’s evaluation on patients. Relevant baseline data will be collected at the time of enrollment in patients with acute ST-segment elevation myocardial infarction reperfusion, mainly including:demography(age, gender, race), medical history, signs, treatment, biochemical values(mainly including serum electrolyte value, serum AST, serum ALT, serum creatinine, serum BUN, serum CK-mb, cTNI, BNP and HsCRP), imaging examination indicators(Echocardiography will be used to measure left ventricular ejection fraction (LVEF), left ventricular end diastolic diameter(LVEDD), global longitudinal strain, myocardial stress changes in each segment and synchrony of myocardial motion, left ventricular contrast echocardiography will assess coronary microcirculation), relevant scale scores(mainly will include 6-minute walk test, Canada Cardiovascular Society (CCS) angina classification, Seattle angina scale (SAQ) score, quality of life scale (SF-8)) (Appendix D) and expression level of miR-140-3p in endothelial progenitor cell (EPCs)-derived exosomes in peripheral blood;Biochemical values, imaging parameters, scores of relevant scales, expression level of miR-140-3p in endothelial progenitor cell (EPCs)-derived exosomes and major adverse cardiovascular events (which will include all-cause death, readmission due to cardiovascular disease, cardiac death, myocardial infarction, heart failure, arrhythmia, emergency coronary revascularization and stroke) will be collected in the test group and control group at 1, 4, 6, 12 and 24 months.

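### Quantitative outcomes, including the LVEF on which the trial is sized, are compared without baseline adjustment although baseline values are collected: valid, but less precise than the data allow

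*Protocol*

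**What the plan says.** The Data analysis section of the protocol sets one general rule per type of variable. For quantitative data, "between-group comparisons will use Welch's t-test or Wilcoxon's rank-sum test". For the rest, "categorical data will be presented as frequencies or percentages, and between-group comparisons will use the chi-square test" or Fisher's exact test. Cox regression appears only with the time-to-event methods. The section names no ANCOVA, mixed model, change score or ordinal method, and sets one threshold: "with P values less than 0.05 considered statistically significant".

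Under Data collection and follow-up, "Relevant baseline data will be collected at the time of enrollment in patients with acute ST-segment elevation myocardial infarction reperfusion". The baseline list includes LVEF, LVEDD, global longitudinal strain, the 6-minute walk, CCS class, SAQ, SF-8 and exosomal miR-140-3p. Imaging measures, scale scores and miR-140-3p then "will be collected in the test group and control group at 1, 4, 6, 12 and 24 months". Each of these outcomes therefore has a baseline value of the same measure.

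Sample size estimation is built on LVEF: "the average LVEF in the control group is 58.0 ± 11.7 points", and "LVEF in the shock wave intervention group can be increased by 8.1%,α= 0.05, and the assurance is 90" per cent. It arrives at 44 evaluable and 51 enrolled per arm, allowing for 15% loss. Under the study objectives, cardiac structure and function, angina and quality of life are secondary. The primary endpoint is a 2-year clinical composite.

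**The concern.** A two-sample test on follow-up values leaves all the between-patient variation in the outcome as noise. Part of that variation is already present at enrolment and can be removed by using the baseline value as covariate. If the correlation between baseline and follow-up is r, and the two arms share it, the residual variance falls by the factor 1 − r². The cost is one degree of freedom.

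Adjustment also corrects the estimate for whatever baseline difference chance produces. That is useful here because allocation is by coin toss, with no stratification described, in about 102 patients.

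At stake is the precision of the secondary quantitative outcomes, above all LVEF, for which the sample size was chosen. This is a method that the protocol states, and not a detail it leaves open.

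**Working it through.** **Inputs from the protocol.** SD of LVEF 11.7 points; difference 8.1, read as absolute points; α = 0.05, taken as two-sided; power 90%; "The test group and the control group will be divided into 1:1 proportional grouping"; 44 evaluable and 51 enrolled per arm; 15% loss.

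**Assumed input.** The baseline-to-follow-up correlation r is not in the protocol. Values of 0.3, 0.5 and 0.7 are used to show a range. The SD is taken as 11.7 at baseline and at follow-up.

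**Step 1: the protocol's own figure.** For an unadjusted comparison of two means,

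n per arm = 2 × [(1.960 + 1.282) × 11.7 / 8.1]² = 43.8, so 44.

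This matches the stated 44. A one-sided test would give 36, and reading 8.1% as relative (0.081 × 58.0 = 4.7 points) would give 131. The stated size therefore corresponds to an unadjusted, two-sided comparison of 8.1 absolute points.

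**Step 2: evaluable number.** 51 × 0.85 = 43.35, so about 43 per arm.

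**Step 3: power at 43 per arm** (two-sided t-test, α = 0.05).

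- Unadjusted: SD = 11.7, standardised difference 8.1 / 11.7 = 0.692, power 88.7%.
- ANCOVA: residual SD = 11.7 × √(1 − r²).
- Change from baseline: SD = 11.7 × √(2(1 − r)).

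| Assumed r | Residual SD, ANCOVA | Power, ANCOVA | SD of change | Power, change score | Power, unadjusted |
|---|---|---|---|---|---|
| 0.3 | 11.16 | 91.4% | 13.84 | 76.5% | 88.7% |
| 0.5 | 10.13 | 95.6% | 11.70 | 88.7% | 88.7% |
| 0.7 | 8.36 | 99.3% | 9.06 | 98.4% | 88.7% |

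ANCOVA gains 2.7, 6.9 and 10.6 percentage points over the unadjusted test. The residual variance falls by 9%, 25% and 51%. The change score is worse than the unadjusted test at r = 0.3, equal at 0.5 and better at 0.7, and ANCOVA is ahead of it throughout. The degree of freedom spent on the covariate is ignored, which is immaterial at this size.

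**Step 4: a smaller effect.** Power near 90% leaves little room to rise, so the gain is larger when the true effect is smaller. If the 8.1% were relative (4.7 points), power at 43 per arm would be about 45% unadjusted, against 57% at r = 0.5 and 73% at r = 0.7 with ANCOVA.

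**The case against.** The best defence is that nothing here is wrong. Welch's test and the rank-sum test are valid under randomisation, and the type I error rate already allows for chance imbalance. The analysis also agrees with the sizing, because 44 per arm is the right number for an unadjusted test. All of this stands, and it limits the point to precision.

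Second, the gain depends on a correlation that the protocol does not give. Treatment starts 2 to 3 days after PCI, and the Introduction itself mentions myocardial stunning, so early LVEF may predict later LVEF poorly. A high r cannot be taken for granted. This also stands, and it is why a range is shown. At r = 0.3 the gain in LVEF power is under 3 points.

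Third, the secondary endpoints are worded as improvement, so the named tests might be meant for change from baseline, which would use the baseline value. The protocol does not say so. If it were so, the advantage of ANCOVA at r = 0.7 would shrink to about 1 point (99.3% against 98.4%). At r = 0.5 it would still be about 7 points, and at r = 0.3 about 15. The recommendation therefore holds under either reading.

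Two stronger readings are tempting:

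- **CCS grade is to be tested by chi-square, so its order is ignored.** The protocol never makes that assignment. It calls CCS a classification but lists it among the scale scores, beside the 6-minute walk, SAQ and SF-8. The rank-sum test it names for quantitative data respects order. All that can be said is that the test for CCS is not assigned.
- **LVEF will be tested separately at five visits, each at 0.05.** The protocol gives five collection times but does not say that each is tested. A false-positive rate computed on that basis would measure a plan the document does not contain.

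**Conclusion.** The point holds as a matter of efficiency. The protocol fixes unadjusted two-sample tests for its quantitative outcomes, names no baseline covariate, and collects the covariate that would sharpen each comparison. For LVEF at 43 per arm, adjustment raises power from 88.7% to between 91.4% and 99.3% for r from 0.3 to 0.7, with more to gain if the true effect is below 8.1 points. These figures rest on the protocol's SD and difference, the absolute reading of 8.1, equal SDs at the two times, and the assumed correlations. The size of the gain for the other quantitative outcomes cannot be calculated, because the protocol gives no SD, effect or correlation for them. The reasoning is the same.

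A reader might infer that the planned tests are invalid or inflate type I error, or that LVEF is underpowered because of them. The documents support none of these, since the planned power is very nearly delivered on the protocol's own inputs. The primary composite, for which time-to-event methods are provided, is untouched. The missing assignment for CCS grade is a minor gap.

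**What to change.** In Data analysis, state that each quantitative outcome is analysed by ANCOVA of the follow-up value on treatment arm, with the baseline value of the same measure as covariate. An equally good choice is one mixed model over 1, 4, 6, 12 and 24 months with baseline, arm, visit and arm-by-visit interaction. Report the adjusted difference with its 95% confidence interval, and keep Welch's test or the rank-sum test as a sensitivity analysis.

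Add one sentence on CCS grade: it is analysed by a method that respects its order, either the rank-sum test already named or proportional-odds regression adjusted for baseline grade.

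The cost is a change of wording. No further patients, visits or measurements are needed, and SPSS, which the protocol already names, fits these models. The change should be made before outcome data are compared by arm, so that the choice of model cannot be influenced by the result.

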**Methodology**

**Study aim and objectives**

This study is order to provide a new therapeutic method for patients with myocardial ischemia-reperfusion injury and reveal the possible mechanism of ECSW for ischemia-reperfusion injury.

The objectives of the study as follows:

**I.** The primary endpoint of this study is 2-year all-cause death, rehospitalization due to cardiovascular disease, major adverse cardiovascular and cerebrovascular events, including cardiac death, myocardial infarction, heart failure, arrhythmia, emergency coronary revascularization, and stroke;

**II.**Secondary endpoints are improvement in angina, quality of life, cardiac structure and function, coronary microcirculation, and expression level of endothelial progenitor cell-derived miR-140-3p.

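### One P < 0.05 rule covers every comparison, while about 11 unranked secondary measures at five visits leave up to 55 openings for a chance significant result; secondary claims are affected, the primary endpoint is not

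*Protocol*

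**What the plan says.** All references are to the protocol.

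- **Data analysis** names two-group tests for quantitative and categorical data, and survival methods for time-to-event data. It then sets one threshold for all of them: "with P values less than 0.05 considered statistically significant". It gives no ranking, adjustment or exploratory label, and it does not say at which visit a measure is compared.
- **Study aim and objectives** separates a primary clinical endpoint at 2 years from the rest: "Secondary endpoints are improvement in angina, quality of life, cardiac structure and function, coronary microcirculation, and expression level of endothelial progenitor cell-derived miR-140-3p". The five domains carry no order and no time point.
- **Data collection and follow-up** lists the variables behind those domains and states that they "will be collected in the test group and control group at 1, 4, 6, 12 and 24 months".
- **Sample size estimation** is built on LVEF, with "the average LVEF in the control group is 58.0 ± 11.7 points" and "α= 0.05, and the assurance is 90" per cent. It describes LVEF only as one among the outcomes observed, and names no visit for it.

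**The concern.** The threshold is a stated rule, not a gap. Read with the two lists above, it allows any secondary measure at any visit to be called significant, and the choice of which to report can be made after the data are seen. This applies to LVEF as well: the sample size rests on a difference in LVEF, yet that difference could be claimed at month 1, 4, 6, 12 or 24.

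At stake is how a sentence such as 'shock wave significantly improved this measure at this month' can be read. For a single comparison fixed in advance, a nominal P < 0.05 has its usual meaning. When it is the best of several dozen, the reader cannot tell it from chance.

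**Working it through.** **1. The plan's own figure.** Inputs from Sample size estimation: SD 11.7; difference 8.1 ("It is estimated that LVEF in the shock wave intervention group can be increased by 8.1", followed by a percent sign); α 0.05; power 90%; 1:1 allocation.

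n per arm = 2 × (1.960 + 1.282)² × 11.7² / 8.1² = 43.8, rounded up to 44. This matches "considering 1:1 randomization, that is, 44 cases in the intervention group and 44 cases in the control group". A one-sided test would give 36, and reading 8.1% as relative (0.081 × 58.0 = 4.7 points) would give 131. So the plan's 0.05 is two-sided and its 8.1 is in absolute LVEF points. Hence, under no effect, each test has a 5% chance of significance in either direction and 2.5% in favour of shock wave.

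**2. Number of comparisons.** From Data collection and follow-up:

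| Group | Measures | Count |
| --- | --- | --- |
| Echocardiography | LVEF, LVEDD, global longitudinal strain, segmental stress, synchrony | 5 |
| Contrast echocardiography | microcirculation | 1 |
| Scales and walk test | 6-minute walk, CCS, SAQ, SF-8 | 4 |
| Exosome marker | miR-140-3p | 1 |
| **Total** | | **11** |

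11 measures × 5 visits = 55. The count is approximate. Leaving out the walk test, which is not assigned to a domain, gives 50. Counting segments or biochemical values separately gives more than 55.

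**3. Independent tests, no true effect.**

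- Expected significant results among 55: 55 × 0.05 = 2.75.
- At least one of 55, either direction: 1 − 0.95^55 = 0.940. Favouring shock wave: 1 − 0.975^55 = 0.752.
- At least one of 11 (one visit), either direction: 1 − 0.95^11 = 0.431. Favouring shock wave: 1 − 0.975^11 = 0.243.

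**4. Correlated tests.** Repeated visits on the same patients, and several indices of the same ventricle, will be correlated. The protocol gives no correlations, so these are assumptions. Test statistics were simulated as normal with constant correlation between visits and between measures; the correlation for a different measure at a different visit is the product of the two. There were 200,000 runs per setting.

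| Assumed correlation (visits / measures) | 55 tests, either direction | 55 tests, favouring shock wave | 11 tests at one visit, either direction | 11 tests at one visit, favouring shock wave |
| --- | --- | --- | --- | --- |
| 0 / 0 | 94% | 75% | 43% | 24% |
| 0.6 / 0.3 | 81% | 48% | 37% | 19% |
| 0.8 / 0.5 | 61% | 31–32% | 30% | 15% |

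At an extreme of 0.9 / 0.7, the 55-test figures fall to 39% and 19%. The comparison for every cell is 5% (either direction) or 2.5% (favouring shock wave) for one test named in advance.

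**5. Smallest family.** One measure per domain at one visit gives five tests: 18–23% in either direction and 9–12% favouring shock wave, over the same three settings.

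**The case against.** **The analysis plan may settle this.** Ranking of secondary endpoints and multiplicity rules often sit in a statistical analysis plan, and none is shown here. Their absence from the protocol is therefore no fault, and this point does not rest on it. It rests on the sentence the protocol does contain, which applies one threshold to every comparison. A plan that restricted secondary claims would have to depart from that sentence.

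**Collection is not testing.** This stands. The five visits form a collection schedule, and Data analysis does not say that each is tested. Fifty-five is an upper figure for the measures counted, which is why the one-visit results are given beside it. But no visit is named either, so the choice stays open.

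**A reader might infer that a false benefit is more likely than not.** The figures do not support this. The 94%, 81% and 61% count differences in either direction, including those favouring control. For benefit alone, the chance is below one half in both correlated settings (48% and 31–32%), and it is 15–24% for 11 measures at one visit.

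**A reader might also infer that the trial's main conclusion is compromised, or that its positive claims will rest on secondary tests.** A single primary endpoint is named and lies outside this family. What the report will emphasise is a prediction, not something the protocol states. Unadjusted secondary results are also common and acceptable when presented as supportive; the difficulty is calling them significant under a rule that does not separate them from the primary.

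**Conclusion.** The concern holds for secondary claims. One unadjusted threshold, about 11 measures, five visits and no order among them make a chance significant difference likely if everything is tested: 61–94% in either direction and 31–75% favouring shock wave over the three settings. Restricting to one visit lowers this to 30–43% and 15–24%. Even the lowest one-visit figure for benefit, 15%, is six times the 2.5% of a single test.

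These results assume no treatment effect, a two-sided 0.05 (supported by the reproduced sample size), the count of 11 measures, and correlations that are illustrative because the protocol gives none. The change should be made, but it is not critical to the primary analysis.

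**What to change.** In Data analysis, replace the blanket sentence with these rules:

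1. Two-sided P < 0.05 applies to the primary endpoint.
2. It also applies to LVEF at one visit, as the single key secondary endpoint. The sponsor names that visit before any outcome data are compared.
3. All other measures and visits are reported as between-group differences with 95% confidence intervals, labelled exploratory, with no statement of statistical significance.

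This is a change of wording; it needs no patients, visits or data. The downside is that fewer secondary results can be called significant.

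Stricter control is an option for the sponsor, not a required change. With two ungated tests the chance of at least one false positive is 1 − 0.95² = 9.8% if they are independent. Testing LVEF only after a significant primary would hold it at 5%, but would place LVEF behind a clinical endpoint for which the trial was not sized. Holm across the five domains at the named visit would allow more formal claims. At its strictest step (0.05 / 5 = 0.01), LVEF power with 44 evaluable patients per arm falls from 90% to about 75%: standard error 11.7 × √(2/44) = 2.49, so 8.1 / 2.49 = 3.25, and Φ(3.25 − 2.576) = 0.75.

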**Ethical consideration**

This study was approved by the Institutional Ethics Committee of Kunming Medical University's first affiliated hospital. This trial protocol had been registered in ClinicalTrials.gov Protocol Registration and Results System (PRS) (NCT05624203). The study protocol adhered to the principles of the Declaration of Helsinki. The approval was also obtained from the study hospital. The purpose of the study, data collection procedures, potential risks and benefits, maintenance of confidentiality, and voluntary basis of participation will be clearly explained to the participants. Written informed consent of the participants will be obtained from them. To ensure the participants’ confidentiality during the study, their names will be coded, and the codes will be stored separately to ensure anonymity. All electronic data will be stored by the principal investigator in a password-protected computer in a secured place. The paper records will be kept by the principal investigator in a locked cabinet. The personal data will only be accessed by the principal investigator. In addition, entered data will be cross checked by a second person. All the data collected will be destroyed 5 years after the study is completed.

**Significance of the study**

This study is expected to provide a new therapeutic approach for patients with myocardial ischemia-reperfusion injury and reveal the possible mechanism of ECSW treatment for ischemia-reperfusion injury.

**Appendix C. Flow diagram of the study protocol**

**
[figure not shown]
**

**Appendix D. Study questionnaire**

**The SF-8 rating scale**

|  |  |  |
| --- | --- | --- |

Date: Serial No

1. In general, in the past 4 weeks, do you think your general health status is:

□ excellent □ Very good □ good □ In general □ poor □ Very poor

2. In the past 4 weeks, has your physical condition limited your ability to do general physical activities (such as walking, climbing stairs, etc.)?

□ No restrictions at all □ A little bit limited □ There are some limitations

□ Very limited □ No physical activity

3. During the past 4 weeks, have you had any health problems carrying out your daily tasks, including going to work and doing housework?

□ It's not difficult at all □ Have a little difficulty □ Have some difficulties

□ Have great difficulty □ Unable to perform routine tasks

4. Have you had any physical pain in the last 4 weeks?

□ No pain at all □ I have a slight pain □ Have a slight pain

□ Have moderate pain □ Have severe pain □ I have very severe pain

5. Have you felt energetic in the past 4 weeks?

□ good □ better □ In general □ poor □ Very poor

6. During the past 4 weeks, to what extent have physical or mental health problems affected your social activities with family and friends?

□ Have no effect at all □ Have little effect □ Have some effect

□ Have a great influence □ You can't socialize

7. In the past 4 weeks, have you been troubled by emotional factors such as anxiety, depression, or irritability?

□ Doesn't bother me at all □ Have mild distress □ Have moderate distress

□ Have a great problem □ Extremely troubled

8. Have you had any personal or emotional problems during the past 4 weeks that have prevented you from carrying out your daily work, school, or other activities?

□ It doesn't affect it at all □ Have a little influence □ Have some effect

□ Have a great influence □ Unable to perform daily activities

